#### Secondary outcomes

Severity and duration of symptoms (time taken for all symptoms to resolve, length of hospital and intensive care stay, mortality rate)Acquisition of non-COVID-19 respiratory viral infections, e.g. common cold or flu symptoms in non-COVID-19 positive participantsUsability and acceptability data of nasal and throat spray as prophylaxisEffect on quality-adjusted life years and cost-effectivenessSubsequent familial/household COVID-19 infectionBaseline haematological or questionnaire findings as predictors for acquiring COVID-19 infection or determining severity and/or duration of resultant infectionassociations between symptom severity and/or duration and prognosis with COVID-19

### Assessment, data collection and follow-up

#### Blood testing

Participants will be required to have blood tests taken to determine baseline haematology, biochemistry and clotting parameters through the following blood tests: Full Blood Count (FBC), C-Reactive protein (CRP), Urea and Electrolytes (U&E), Ferritin, Liver function tests (LFT), Lactate Dehydrogenase (LDH), D-dimer and Vitamin D level, which have been suggested as potential surrogate markers of COVID-19 severity [41–49]. These blood investigations will also be repeated at the end of the study period for each participant.

All biological samples will be analysed and stored at Swansea Bay University Health Board.

#### Seroconversion

Participants will be tested for SARS-CoV-2 antibodies using the enzyme-linked immunosorbent assay at the start and end of the study period. The presence of SARS-CoV-2 antibodies at the start of the trial indicates the previous infection with COVID-19 and the participant data will as such be excluded from the trial. Participants will be deemed to have acquired COVID-19 during the study period if they are antibody negative at the start of the study and positive for SARS-CoV-2 antibodies at the end of the study (i.e. seroconversion). This will be an essential means of detecting individuals with asymptomatic infection during the study period.

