### Randomisation

Following consent, baseline data will be collected, and the participants will be issued a randomisation ID which will assign them to either placebo or verum spray. This will be documented on the enrolment log. The randomised spray bottles will be stored at Swansea University, UK, for assignment to subject participants.

Randomisation sequence will be created using R 3.6.3 (R Core Team 2020) based on the pseudorandom number generation algorithm “Mersenne-Twister” using a 10-digit seed for reproduction. Participants will be assigned to the respective treatment with a 1:1 allocation and fixed block size by a statistician with no clinical involvement in the trial.

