#### Baseline assessment

Participant demographics including date of birth, gender and ethnicity will be recorded. Medical history will be recorded including current medical conditions, regular medications, and any allergies. Participants will be asked to complete a quality-of-life questionnaire: EQ-5D-3L, this will also allow for a later cost-effectiveness analysis as well as undergo the baseline blood tests outlined above. Randomisation and training in spray application will take place after baseline assessments and questionnaires have been completed, on the same day.

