#### Adverse events

Adverse events are, according to the definitions, any unfavourable or unintended event affecting participants during the study. In cases of prolongation of hospitalisation, death or significant clinical sequelae, these events are defined as serious adverse events (SAEs), the occurrence of which the study sponsor (Swansea University) will be informed within 48 h of the initial observation of the event. The study treatment period is defined as the period from the first study-related nasal and throat spray administration until 14 days after the last study-related nasal and throat spray administration. Participants will be encouraged from the outset to contact the research team at the time of an event occurring by telephone or email and all details will be documented on the SAE form. The daily symptom tracker questionnaire will also provide an opportunity for symptom monitoring and the opportunity to report any symptoms that will be flagged up to the research team via a weekly report.

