### Statistical analysis

Data will be analysed in accordance with an intention-to-treat analysis. Each of the outcome measures will be checked for the distribution to be normal. Each of the outcome measures and important baseline covariates would be reported along with their missingness. If required appropriate imputation method would be adopted in the main analysis. All the statistical data management and analysis will be done under standard statistical software (e.g. STATA version 16 or IBM SPSS version 26).

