#### Secondary outcomes

Our approach toward the secondary outcome analysis would be mainly exploratory and report the summary outcomes of the secondary outcome measures. We will check the distributions of the data whether following normal or not. For any continuous secondary outcomes (e.g. length of hospital stay, severity and duration of symptoms) we will report the mean and standard deviation, along with the outcome of statistical tests by groups (e.g. *t*-test). The categorical outcomes will be reported using percentages and chi-square tests. In all cases, a summary of the missing data will be reported. We will also report the safety data using summary statistics by the patients and the events for each of the trial arm groups.

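### The exclusion for a positive baseline antibody covers all of a participant's data, although its rationale supports removal only from the COVID-19 acquisition analysis

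*Protocol article*

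**What the plan says.** The Seroconversion section of the protocol article sets the test times: "Participants will be tested for SARS-CoV-2 antibodies using the enzyme-linked immunosorbent assay at the start and end of the study period". For a participant who is positive at the start it states that "the participant data will as such be excluded from the trial". The stated reason is that antibodies at the start show earlier infection. The sentence is not limited to one outcome and exempts nothing.

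Two sections fix the order of events at enrolment. Under Randomisation: "Following consent, baseline data will be collected, and the participants will be issued a randomisation ID". Under Baseline assessment: "Randomisation and training in spray application will take place after baseline assessments and questionnaires have been completed, on the same day". Neither makes randomisation or first use of the spray wait for an antibody result.

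Other sections assume that all participants are kept. Adverse events defines the treatment period as running "from the first study-related nasal and throat spray administration until 14 days after the last study-related nasal and throat spray administration". Statistical analysis says "Data will be analysed in accordance with an intention-to-treat analysis", without qualification. Its Secondary outcomes paragraph promises to "report the safety data using summary statistics by the patients and the events for each of the trial arm groups". Usability and non-COVID-19 respiratory infection are listed as secondary outcomes, and EQ-5D-3L is collected from all participants.

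**The concern.** Being antibody-positive at baseline is a sound reason not to count someone in an analysis that depends on moving from negative to positive. It does not bear on whether the spray causes adverse events, whether people find it usable, or how their quality of life changes. The rule nevertheless applies to the participant's data as a whole.

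If a seropositive participant has been randomised and has begun spraying before the result returns, two parts of the article pull against each other. The Adverse events section counts that person from the first spray, while the Seroconversion section takes the person's data out of the trial. A by-arm safety table built on the second rule would omit people who were exposed. A trial of a prophylactic meant for long-term use in healthy people should report safety on everyone who used it. The usability and quality-of-life comparisons would also lose participants for a reason unrelated to what they measure.

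**Working it through.** **Step 1. Does the rule reach randomised, exposed people?** The sections can be set side by side.

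- The antibody test is an ELISA on blood taken at the start (Seroconversion). The Management of biological samples section lists it among the tests run by the health board.
- Randomisation and training follow the baseline assessments on the same day (Baseline assessment).
- No section holds allocation or first use for the result.
- The rule removes data; it does not declare the person ineligible. That wording fits someone already enrolled.

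Exposure before the result is therefore likely. It remains an inference, because neither the turnaround time nor the date of first use is given.

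**Step 2. Which outcomes need a negative baseline?**

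- COVID-19 acquisition: yes, for the seroconversion component.
- Adverse events, usability, quality of life: no.
- Non-COVID-19 respiratory infection: in part. The Outcomes section describes it as, for example, cold or flu symptoms in participants who are not COVID-19 positive. Seroconversion cannot help to settle that status in someone already positive at the start, so PCR and symptoms would have to do so alone.

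**Step 3. The plan's own sample size.** Inputs from the Sample size section: proportions 0.25 and 0.125, two-sided 5%, 80% power, 20% loss. With pooled variance under the null and no continuity correction:

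n per arm = [1.96 × √(2 × 0.1875 × 0.8125) + 0.8416 × √(0.25 × 0.75 + 0.125 × 0.875)]² / 0.125² = (1.0819 + 0.4586)² / 0.015625 ≈ 151.9, rounded up to 152.

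The total is 304, and 304 / 0.8 = 380. The stated figures reproduce, and the point does not depend on any error in them.

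**Step 4. Scale of the loss.** The article gives no expected seropositive share *s*, so *s* is an assumption. The top value borrows the healthcare-worker seroprevalence quoted in the Sample size section. The formulas are:

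- lost = 380 × *s*
- verum arm left = 190 × (1 − *s*)
- chance of seeing at least one case of a 1% adverse event = 1 − 0.99^(verum arm left)
- standard error ratio = 1/√(1 − *s*)

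| Assumed share | Lost of 380 | Remaining | Verum arm | Chance of seeing a 1% event | Standard error ratio |
|---|---|---|---|---|---|
| 0 | 0 | 380 | 190 | 85.2% | 1.00 |
| 5% | 19 | 361 | 180.5 | 83.7% | 1.03 |
| 10% | 38 | 342 | 171 | 82.1% | 1.05 |
| 24.4% | 92.7 | 287.3 | 143.7 | 76.4% | 1.15 |

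The table treats every seropositive person as randomised, exposed and wholly removed, and ignores other losses.

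**Step 5. Is there bias between arms?** Baseline assessments are completed before randomisation. If the antibody sample is among them, serostatus is a pre-allocation characteristic, and exclusion on it should fall equally on the two arms apart from chance.

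**The case against.** The strongest reply is that the sentence sits under a heading about how infection is ascertained and was probably meant only for that purpose. The Adverse events section and the by-arm safety summary make no exception for serostatus. The planned adjustment for previous COVID-19 also suggests that previously infected people were not to vanish altogether. The article condenses a fuller protocol, the eligibility figure is not shown, and analysis sets are usually defined in the SAP. Much of this is fair, and the absence of a defined safety set is not the point here. What stands is that the article does state a rule, in terms wider than its reason. A SAP that kept these people in a safety set would contradict that rule as written.

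A reader might infer several stronger things that the documents do not support:

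- **That seropositive participants are known to have sprayed before the result.** Timing is not stated. The baseline blood panel under Blood testing does not name the antibody test, so same-day sampling is itself an inference, though a natural one.
- **That their data are erased, or that serious events go unreported.** The rule speaks of exclusion, not erasure. Notification of serious events to the sponsor within 48 hours has no serostatus exemption and would still operate. The gap is in the reported summary.
- **That the treatment comparison is biased.** Step 5 points the other way.
- **That about 93 of 380 is the expected loss.** The 24.4% describes healthcare professionals. The trial initially sought professionals with no previous positive test and later widened to other key workers and people who mix outside their household. Nothing shows that the figure applies to them.
- **That the other-virus outcome is wholly independent of serostatus.** Its wording under Outcomes ties it to not being COVID-19 positive, so it needs separate handling.

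**Conclusion.** The concern holds as a fault of scope. Excluding baseline-positive participants from the COVID-19 acquisition analysis is reasonable. Excluding their data from the trial is not supported by the reason given, and it conflicts with the adverse-event window, the by-arm safety summary and the unqualified intention-to-treat statement.

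The consequence is incomplete safety reporting and some lost precision, without expected bias between arms. At an assumed 5% to 10% seropositive, 19 to 38 people are affected. The chance of seeing a 1% adverse event in the verum arm then falls by about 1.5 to 3 percentage points, and standard errors for usability and quality of life rise by about 3% to 5%. The 24.4% case (about 93 people, 85% down to 76%, standard errors up 15%) is an extreme.

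These sizes rest on the assumed share and on spraying having begun before the result. Usability and quality-of-life losses depend further on how much follow-up these participants complete, which the article does not say. The effect is modest at plausible shares, but the correction is almost free and should be made.

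**What to change.** Replace the sentence in the Seroconversion section with a rule that sets the population for each outcome:

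- **COVID-19 acquisition:** a named baseline-seronegative (modified intention-to-treat) set, with the Statistical analysis section using the same name.
- **Safety:** every randomised participant who used at least one spray, whatever the baseline serostatus.
- **Usability and quality of life:** all randomised participants, with the data available.
- **Non-COVID-19 respiratory infection:** include baseline-seropositive participants, with COVID-19 status classified by PCR and symptoms only, and report a sensitivity analysis in baseline-seronegative participants.

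The cost is a short statement of analysis populations, with no additional tests or participants. The primary analysis still omits baseline-positive participants, so its power is the same as under the present rule. The small downside is that analysis sets differ by outcome, and each must be described and its numbers shown in the participant flow.

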## Strengths and limitations of this study

A randomised placebo-controlled double-blind trialSecondary outcomes designed to improve understanding of the effects of carrageenan nasal and throat sprays on COVID-19 transmission, acquisition, severity and/or duration of resultant infection and other acute respiratory infectionsRoll out of the vaccination programme has reduced the eligible participant population from which to recruit

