### Outcomes

#### Primary outcome

Acquisition of COVID-19 infection as confirmed by a positive PCR swab taken at symptom onset or seroconversion during the study

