### Revision to trial design

The trial protocol was written prior to the introduction of vaccines and was initially aimed to recruit healthcare professionals who have not been previously tested positive for COVID-19. However, the success of the UK vaccination programme and prioritisation of healthcare professionals for vaccines has meant that the majority of staff were no longer eligible for the trial. Approval was therefore sought from the Sponsor (Swansea University), REC and SBUHB (NHS) R&D Office to widen the potential pool of study participants to include all key workers or those needing to interact with people outside of their household for study or work from the 11th of January 2021. The full trial protocol is available on ClinicalTrials.gov [40].

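### The seroconversion rule has no exception for vaccination during follow-up, so if the assay detects vaccine antibody and serology enters the primary analysis, vaccinated uninfected participants become false primary events

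*Protocol article*

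**What the plan says.** The Outcomes section defines the primary outcome as "Acquisition of COVID-19 infection as confirmed by a positive PCR swab taken at symptom onset or seroconversion during the study". The Abstract gives the same definition.

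The Seroconversion section supplies the rule for the serological route. On the assay it says: "Participants will be tested for SARS-CoV-2 antibodies using the enzyme-linked immunosorbent assay at the start and end of the study period". On classification it says: "Participants will be deemed to have acquired COVID-19 during the study period if they are antibody negative at the start of the study". The second condition concerns the exit sample, which has to be "positive for SARS-CoV-2 antibodies at the end of the study (i.e. seroconversion". No target antigen is named and vaccination is not mentioned. Baseline antibody is read in the same way: "The presence of SARS-CoV-2 antibodies at the start of the trial indicates the previous infection with COVID-19".

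The Revision to trial design section says: "The trial protocol was written prior to the introduction of vaccines". It adds that "the success of the UK vaccination programme and prioritisation of healthcare professionals for vaccines has meant that the majority of staff were no longer eligible", and that recruitment was widened from 11 January 2021. It reports a change of population but none to the serology rule. The Strengths and limitations section confirms that roll-out of the "vaccination programme has reduced the eligible participant population from which to recruit".

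Three other sections bear on the point:
- End of study treatment places the exit serology at the end-of-study visit. The Quality of life and Usability sections put study end at week 10; the spray is used for 8 weeks.
- Statistical analysis, Primary outcome, describes the analysed variable as confirmation by PCR swab and does not mention seroconversion.
- Management of biological samples says that samples are disposed of after analysis and that none are kept.

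**The concern.** The Seroconversion section treats infection as the only source of SARS-CoV-2 antibody. That was a fair premise before vaccines existed. It is no longer one for a trial that, by its own account, recruits from the shrinking group of people not yet vaccinated and takes exit serology some 8 to 10 weeks later. The text implies that vaccinated people are ineligible at entry, but that does not cover vaccination after randomisation.

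An uninfected participant who is vaccinated in that window, and whose antibody the ELISA detects, meets the written definition of a primary event. Such events have nothing to do with the spray. They add background to both arms, pull the risk ratio towards 1 and cost power. What is at stake is a false-negative conclusion about a spray that works.

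**Working it through.** **1. Inputs.** From Sample size: rates of 25% and 12.5%, two-sided 5%, 80% power, 152 per arm (304), 20% loss, 380 in total. That section attaches the 25% to the intervention arm; the power calculation is the same whichever arm holds which rate, and 25% is taken below as the placebo rate. From Outcomes and Seroconversion: either PCR or seroconversion makes an event. Assumed, because the documents give no figure: v, the share of otherwise uninfected participants in each arm who turn antibody positive through vaccination by the exit sample. It is taken as equal in both arms because treatment is blinded.

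**2. The plan's own figure.** Pooled two-proportion formula without continuity correction, mean rate 0.1875:

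n = [1.96·√(2·0.1875·0.8125) + 0.8416·√(0.25·0.75 + 0.125·0.875)]² / 0.125² = 151.9, so 152 per arm.

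Power at 152 per arm is 80.0%, and 304/0.8 = 380. The stated figures reproduce.

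**3. Effect of the rule.** A participant counts if infected, or if uninfected but vaccine-seropositive:

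p′ = p + (1 − p)·v

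The difference becomes (p₁ − p₂)(1 − v), so it shrinks while the background rises. At v = 20%: 0.25 + 0.75·0.20 = 40.0% and 0.125 + 0.875·0.20 = 30.0%. The difference falls from 12.5 to 10.0 points and the risk ratio moves from 0.50 to 0.75. The false events number 152·0.75·0.20 = 22.8 and 152·0.875·0.20 = 26.6, so slightly more fall in the arm with fewer infections.

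| v (assumed) | Rates | Risk ratio | Power, 152 per arm | Total N for 80% power, before dropout |
|---|---|---|---|---|
| 0 | 25.0% vs 12.5% | 0.50 | 80.0% | 304 |
| 5% | 28.8% vs 16.9% | 0.59 | 69.6% | 390 |
| 10% | 32.5% vs 21.3% | 0.65 | 60.0% | 486 |
| 20% | 40.0% vs 30.0% | 0.75 | 44.7% | 712 |
| 30% | 47.5% vs 38.8% | 0.82 | 33.7% | 1004 |

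**4. Type I error.** If the spray has no effect, p is the same in both arms. With equal v, p′ is then also the same, so the test keeps its level. The error is one of dilution only.

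**5. Which endpoint is analysed.** Under the Outcomes and Seroconversion sections, v enters the primary test as above. Under the PCR-only wording in Statistical analysis it does not, and the loss in the table does not arise. Both cannot stand. The Seroconversion section calls serology essential for detecting asymptomatic infection, which argues against reading the PCR-only sentence as a deliberate narrowing.

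**The case against.** The strongest reply is that this is a condensed article. The eligibility figure is not shown and the full protocol is held elsewhere. Assay antigen, recording of vaccination and handling of events after randomisation are often settled there or in the SAP, and their absence here proves nothing. That stands as far as it goes: nobody can say from this text that vaccination goes unrecorded, or that the assay reacts to vaccine antibody. It does not rescue the rule. The article does not merely leave a detail out; it states a complete classification rule that is wrong for a vaccinated, uninfected participant whose antibody the assay detects. A different rule elsewhere would contradict it.

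The harm also needs several conditions: a vaccine-reactive assay, vaccination early enough to show at exit, and seroconversion in the primary analysis. All of that stands and limits how firmly the size can be stated.

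Three stronger readings are tempting, and the documents do not support them:
- A reader might infer that the trial will largely measure vaccine uptake. No uptake rate or assay target is given, so this is possible but not shown.
- A reader might infer a spurious benefit. Under blinding the false events should be roughly balanced, and the bias runs towards no effect.
- A reader might take lower attack rates and find power near zero. At 5% vs 2.5% with v = 20%, power is 6%. But those rates are not in the protocol, and power is already 20.8% with no vaccination at all, so most of the shortfall from 80% comes from the low attack rate.

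**Conclusion.** The point holds in conditional form. As written, any change from antibody negative to positive is acquired COVID-19, in a trial that enrols unvaccinated people during roll-out. If the ELISA detects vaccine-induced antibody, and if seroconversion is part of the analysed primary outcome, participants vaccinated during follow-up become false primary events in both arms. The consequence is dilution and lost power, with the type I error intact.

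On the planned rates and 152 per arm, even v = 5% costs about ten points of power (80% to 70%), and v = 20% brings it to 45%. Every v is an assumption, and these figures rest also on equal vaccination in the two arms. The fault in the rule can be read directly from the text; the size of the damage cannot.

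**What to change.** - Reconcile Outcomes, Seroconversion and Statistical analysis on whether seroconversion is part of the primary outcome, and use one definition throughout.
- Reword the Seroconversion rule so that a positive exit sample counts only for an antibody that the vaccine received does not induce (for example nucleocapsid, where the vaccine does not contain it), with a negative baseline on the same assay. Name the assay target.
- Record the date of every vaccine dose.
- Where only a vaccine-reactive result exists, do not count antibody positivity after a vaccination as an event. Let PCR events count, and treat the serology as missing.
- Add a sensitivity analysis that ends follow-up at the first vaccine dose.

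The cost is an assay specification, one data item, and protocol and SAP wording. It is not free for everyone: because no samples are kept, a baseline on the new assay may be unobtainable for participants already tested on another one, and they fall under the vaccine-reactive provision if they are vaccinated. The downside is that serology tells less in vaccinated participants, so some asymptomatic infections among them will be missed. If vaccine-explained positivity is kept out (v = 0), the stated 304 and 380 need no change on this account, provided that the assumed event rates still hold.
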